### Statistical Analysis

The primary outcome is 30-day inpatient mortality compared between the usual care and intervention arms using intention-to-treat analysis (ie, all patients randomized to intervention vs usual care regardless of whether the intervention resulted in a change in fluid choice). The outcome of 30-day inpatient mortality is measured for the index hospitalization. Readmissions and subsequent deaths are not counted toward the primary outcome for the initial hospitalization, but are considered for the readmission hospitalization. The primary analysis will be an assessment for a difference in 30-day inpatient mortality between the arms with a 2-sided *z* test with continuity correction and pooled variance. Thirty-day inpatient mortality rates will be determined using 95% CIs within each study arm and for the observed difference between study arms.

The secondary analysis for primary and secondary outcomes will be a generalized mixed-effects linear model (ie, log-binomial regression model) to estimate the outcome, adjusted for baseline characteristics including age, sex, race and ethnicity, and Sequential Organ Failure Assessment (SOFA) score at randomization. Race and ethnicity will be included in the analyses given potential disparities in treatments and health outcomes by race. The model will also be adjusted for month of the trial, with an interaction term between month and treatment allocation, to evaluate for temporal trends in the efficacy of the intervention (eg, increasing use of balanced crystalloids in usual care could result in decreased separation of the study arms). The hospital to which the patient is admitted will be defined as a random effect (random intercept) in the mixed model. In a separate sensitivity analysis, the hospital to which the patient is admitted will be defined as a fixed effect to evaluate the robustness of the findings. The covariate-adjusted 30-day inpatient mortality rates will be determined using 95% CIs for each study cohort and for the observed difference between the usual care and intervention arms in 30-day inpatient mortality rates. Relative risks will be calculated to measure the degree of association between individual risk factors and 30-day inpatient mortality. The SAS GLIMMIX Procedure, version 9.4 (SAS Institute Inc) will be used to implement the log-binomial regression model.

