### Subgroup Analyses for 30-Day Inpatient Mortality

The heterogeneity of intervention effects across levels of a baseline variable will be investigated using a statistical test for interaction.^15^ The effect of intervention on 30-day inpatient mortality will be evaluated by the following prespecified subgroups: age, sex, severity of illness (quartiles of SOFA), and kidney injury on hospital presentation (KDIGO stage <2 [less severe] vs KDIGO stage ≥2 at enrollment). Effect of intervention in subgroups will be determined by including the interaction between the intervention and subgroup in the log-binomial regression model. Sensitivity analysis will be performed on patients with presence of sepsis defined by *International Statistical Classification of Diseases and Related Health Problems, 10th Revision* coding on discharge.

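### The only adjusted model carries a treatment-by-month interaction, and no overall treatment contrast is defined from it for the secondary outcomes

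*Protocol article*

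**What the plan says.** The primary analysis in the Statistical Analysis section is unadjusted: a "2-sided *z* test with continuity correction and pooled variance". It has no month term.

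The adjusted analysis follows: "The secondary analysis for primary and secondary outcomes will be a generalized mixed-effects linear model (ie, log-binomial regression model) to estimate the outcome". Covariates are age, sex, race and ethnicity, and SOFA score, with hospital as a random intercept. To this the section adds: "The model will also be adjusted for month of the trial, with an interaction term between month and treatment allocation". The stated purpose is "to evaluate for temporal trends in the efficacy of the intervention", with rising use of balanced crystalloids in usual care given as an example.

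Two summaries from the model are named. The first is for mortality only: "The covariate-adjusted 30-day inpatient mortality rates will be determined using 95% CIs for each study cohort and for the observed difference". The second is "Relative risks will be calculated to measure the degree of association between individual risk factors and 30-day inpatient mortality", which does not name treatment.

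No adjusted model without the interaction is described. The hospital sensitivity analysis only changes hospital from a random to a fixed effect. The Subgroup Analyses section works by "including the interaction between the intervention and subgroup in the log-binomial regression model". The coding of month (linear or categorical, centred or not) is not given.

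**The concern.** Whether the alert works and whether its effect drifts over the year are two questions, and the plan puts both into one model. Once treatment-by-month is included, the treatment coefficient no longer has a fixed meaning. With linear uncentred month it is the log relative risk at month 0. With categorical month and reference-cell coding it is the log relative risk in one month. Only with centred or effect-coded month does it come close to an average over the trial.

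This matters most for the secondary outcomes: ICU admission, in-hospital mortality, vasoactive drugs, new kidney replacement therapy and mechanical ventilation. The z test covers only the primary outcome, so this model is their only stated comparison between arms, and no overall contrast is defined from it. A relative risk taken from the default output could be imprecise. If the effect fades, as the plan itself anticipates, it could also be off target. It might then appear to disagree with the primary result for no reason other than coding.

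**Working it through.** **Inputs.** From Sample Size and Power Considerations: 6% usual care, 3% intervention, 1001 per arm, 90% power. From Interim Analysis: final two-sided 0.05. From Randomization and Allocation: 1:1. From Study Design: at least 12 months of enrolment. Assumed: exactly 12 months, even accrual, and risks constant over time unless stated.

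**The plan's own figure.** The pooled-variance formula without continuity correction is n = [1.960·√(2·0.045·0.955) + 1.282·√(0.03·0.97 + 0.06·0.94)]² / 0.03². It gives 1002 after rounding up, against the stated 1001, so the inputs are read correctly.

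**Trial-level effect.** The variance of the log RR is 0.97/(1001·0.03) + 0.94/(1001·0.06) = 0.0323 + 0.0157 = 0.0480, so SE = 0.219. With |log 0.5| = 0.693, power = Φ(0.693/0.219 − 1.96), about 89%.

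**Treatment coefficient with the interaction kept.** For linear month the SE is multiplied by √(1 + mean²/variance) of the month codes. The variance of 12 equally spaced codes is 143/12 = 11.92. For categorical month with one reference month the multiplier is √12.

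| Coding of month | Multiplier | SE of log RR | Power for RR 0.5 |
|---|---|---|---|
| No interaction | 1 | 0.219 | about 89% |
| Linear, 0–11 | √(1 + 5.5²/11.92) = 1.88 | 0.412 | about 39% |
| Linear, 1–12 | √(1 + 6.5²/11.92) = 2.13 | 0.467 | about 32% |
| Categorical, one reference month | √12 = 3.46 | 0.759 | about 15% |

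Under these assumptions the multipliers do not depend on the event rate, so they carry over to the secondary outcomes. The power figures do not, because the protocol gives no event rates for those outcomes.

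**Simulation check.** In 1000 simulated trials (log-link Poisson with robust SE standing in for log-binomial, no covariates or hospital effect), all with the interaction kept:
- Uncentred coefficient (month 1–12): mean SE 0.474, significant in 31%.
- Centred-month coefficient: mean SE 0.225, significant in 91%.
- Risk difference standardised over enrolled patients' months: mean −0.030, SE 0.009, significant in 92%.

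The loss therefore comes from what is read off the model, not from the term being in it.

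**If the effect fades.** Take a hypothetical log-linear fade to RR 1 at month 12, with usual care at 6% and average intervention mortality of 3%, so the trial-average RR is 0.50. The effect at month 1 is then RR 0.19 and the month-0 coefficient corresponds to RR 0.17. At the mean month it is 0.44, close to the average but not equal to it.

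**Sparse months.** With categorical month there are 1001/12 = 83.4 intervention patients a month, and 83.4·0.03 = 2.5 expected deaths. The chance of no deaths in a given intervention month is 0.97^83.4 = 0.079. The chance of at least one such month in 12 is 1 − (1 − 0.079)^12 = 63%. A month-by-treatment term for such a month has no finite estimate on the log scale.

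**Subgroup tests.** In a simulation with a 50/50 subgroup and RR 0.3 versus 0.7, the SE of the treatment-by-subgroup term was 0.484 both with and without linear treatment-by-month, and power was 42.2% versus 42.0%.

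**The case against.** The strongest reply is that the protocol never says the treatment coefficient will be reported as the effect. For 30-day mortality it plans adjusted rates by arm and their difference. Standardised over enrolled patients' months, that is a trial-level effect with no material loss of power. This stands, and it removes most of the force for mortality. What remains there is that the averaging over months is unstated. It does not help the secondary outcomes, for which no such summary is named.

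A second reply is that coding and post-estimation contrasts normally belong in the statistical analysis plan, which is not shown. That is fair for the coding, and missing coding is not the point here. The point is a model choice the article does state: one adjusted model, with the drift term inside it, and none without.

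A third is that looking for drift is sensible, since the Limitations section names changing baseline practice. Agreed; the issue is only where the term sits.

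A reader might go further and infer that the trial's adjusted result will be a month-zero estimate, that the main conclusion is at risk, or that the subgroup tests lose power. The documents support none of these. The coding is not given, the primary z test has no month term, and the subgroup interaction is not redefined by also having treatment-by-month in the model. Nor does the text say that the subgroup models keep the month interaction.

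**Conclusion.** The concern holds for the secondary analyses and is of moderate weight. The only adjusted model, which is also the only stated between-arm analysis of the secondary outcomes, includes an interaction that leaves the meaning of its treatment coefficient dependent on coding. Under uncentred linear or reference-month coding, a relative risk read from it would have an SE 1.9 to 3.5 times that of the trial-level effect. For mortality, power would be about 15% to 39% against about 89%. Under centred coding or month-standardised rates there is no material loss. Categorical month adds a separate risk that the interaction model cannot be estimated.

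These sizes rest on 1001 per arm, 6% versus 3%, 12 evenly filled months and constant risks. The fade example is hypothetical. The 89% belongs to a Wald test of the log relative risk in a secondary model; the trial's 90% design power belongs to the primary test and is intact.

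**What to change.** Preferred: for every outcome, estimate the adjusted effect from the log-binomial model with month as a main effect only. Fit a second model with treatment by linear month (1 degree of freedom) solely to test and display drift.

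Alternative, if one model is kept: define the reported effect for every outcome, secondary outcomes included, as the risk difference and relative risk with 95% CI standardised over the enrolled patients' months. State that the treatment coefficient is not the reported effect, and keep month linear within the interaction so that months without deaths do not break the fit.

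The subgroup interaction tests need no change on this account. The cost is a few sentences of wording and, under the preferred option, one extra model fit per outcome, with no change to data collection or sample size. It should be settled before the final outcomes are analysed by arm, so that the choice cannot appear to follow the results.

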### Randomization and Allocation

Patients will be randomized to usual care vs intervention using software within the EHR in a simple 1:1 ratio without stratification. Randomization occurs at the point of clinicians initiating a normal saline order.

For patients randomized to the intervention arm, the EHR alert will fire in the ED and the ICU every time normal saline is ordered until the first of the following events: ICU discharge, death, or 30 days of hospitalization. The study intervention will not be continued in the wards. For patients randomized to the usual care arm, there will be no EHR alert in response to fluid orders.

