### Concealment and Blinding

The PRECISE study is single-blind (ie, patients are blinded to the allocation). In the usual care arm, the clinicians will not receive any feedback from the algorithm and will not know the group classification of their patient. In the intervention arm, if a clinician orders normal saline in a patient classified as having group D sepsis, there will be an EHR alert and the clinician will necessarily be unblinded to the allocation.

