### Outcomes

The primary outcome is 30-day inpatient mortality. Secondary outcomes include ICU admission, in-hospital mortality, receipt of vasoactive drugs, receipt of new kidney replacement therapy, and receipt of mechanical ventilation (vasoactive drugs, kidney replacement therapy, and mechanical ventilation are counted if they occur after randomization and within the 30-day study period). Process outcomes include volume of normal saline and percentage of alerts accepted.

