The process outcome of volume of normal saline administered per patient will be compared in unadjusted analysis between the intervention and usual care arms. The total number of alerts generated and the percentage of alerts accepted in the intervention arm will be reported.

Secondary analysis of the primary outcome will be performed on the subset of randomized patients who were admitted to the ICU and thus would have potential exposure to intervention in both the ED and ICU settings. Any additional outcomes or analyses will be clearly identified as post hoc and will be considered hypothesis-generating.

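### The ICU-admitted and discharge-coded sepsis analyses select patients on events settled after randomization, so their mortality contrasts should be reported as descriptive only

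*Protocol article*

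**What the plan says.** All references are to the Protocol article.

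- **Randomization and Allocation:** "Randomization occurs at the point of clinicians initiating a normal saline order". In the intervention arm, "the EHR alert will fire in the ED and the ICU every time normal saline is ordered", so the alert is already active before transfer to the ICU.
- **Concealment and Blinding:** when an intervention-arm clinician orders normal saline, "there will be an EHR alert and the clinician will necessarily be unblinded to the allocation".
- **Outcomes:** "Secondary outcomes include ICU admission".
- **Statistical Analysis, primary:** the comparison covers "all patients randomized to intervention vs usual care regardless of whether the intervention resulted in a change in fluid choice".
- **Statistical Analysis, ICU subset:** a secondary analysis of the primary outcome is to be "performed on the subset of randomized patients who were admitted to the ICU and thus would have potential exposure to intervention" in both settings.
- **Subgroup Analyses for 30-Day Inpatient Mortality:** "Sensitivity analysis will be performed on patients with presence of sepsis defined by" ICD-10 codes at discharge. The same section frames effect heterogeneity around baseline variables and lists SOFA quartiles among its subgroups.

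The hypothesis-generating label in Statistical Analysis is attached only to analyses added later. It does not reach these two, and neither carries a caveat about selection after randomization.

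**The concern.** Randomization makes the arms comparable at the normal saline order. A subset keeps that comparability if it is defined by something fixed at or before that moment. ICU admission and discharge coding are both settled later, once allocation has had a chance to act.

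For ICU admission the difficulty is built into the plan: the trial tests whether the alert changes it and also conditions on it. There are two routes from allocation to admission. One is the fluid given in the ED. The other is the behaviour of a clinician who has been told that the patient belongs to a group with a mortality signal. If either route is active, the ICU patients in one arm are a different mix from those in the other.

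At stake is how two prespecified results are read. An alert that usefully averts ICU stays in milder patients would leave a sicker ICU group and could look harmful there. One that prompts more admissions of milder patients could look beneficial with no effect on death.

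**Working it through.** **Step 1. Timing of each selecting variable against randomization**

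| Variable | When settled | Can allocation act first? | Other role in the plan |
|---|---|---|---|
| SOFA at randomization | At randomization | No | Model covariate; SOFA quartiles are a subgroup |
| ICU admission | After the ED saline order, for patients exposed in both settings | Yes: alert active in the ED, clinician unblinded | Secondary outcome |
| ICD-10 sepsis coding | Discharge | Yes: the whole stay precedes it | None |

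Only the first row is a baseline variable in the sense used in the plan's subgroup section.

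**Step 2. The plan's own figure**

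No size is stated for either subset. The only relevant figure is 1001 per arm for 6% vs 3% at 90% power (Table 1). With pooled variance and no continuity correction, and mean rate 0.045:

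n = [1.960·√(2·0.045·0.955) + 1.282·√(0.06·0.94 + 0.03·0.97)]² / 0.03² ≈ 1002

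This reproduces the stated figure to within one patient. It refers to all randomized patients and does not depend on the point made here.

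**Step 3. Illustration for the ICU subset**

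Every input in this step is an assumption except the 6% overall mortality, which matches the usual-care rate in Sample Size and Power Considerations.

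- Severe patients: 20% of those randomized, death 20%, ICU admission 80% in both arms.
- Milder patients: 80% of those randomized, death 2.5%, ICU admission *a*, with *a* = 30% in usual care.
- Within a stratum, death does not depend on ICU admission.
- Overall mortality: 0.2·0.20 + 0.8·0.025 = 6%.

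ICU-only mortality is M(a) = (0.2·0.8·0.20 + 0.8·a·0.025) / (0.2·0.8 + 0.8·a) = (0.032 + 0.02a) / (0.16 + 0.8a).

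Usual care: M(0.30) = 0.038/0.40 = 9.5%.

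Now let the alert have no effect on death and change only *a* in the intervention arm:

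| *a*, intervention | ICU share | ICU-only mortality | Difference, points | ICU-only RR | All-randomized RR |
|---|---|---|---|---|---|
| 15% | 28% | 0.035/0.28 = 12.5% | +3.0 | 1.32 | 1.00 |
| 20% | 32% | 0.036/0.32 = 11.25% | +1.75 | 1.18 | 1.00 |
| 25% | 36% | 0.037/0.36 = 10.3% | +0.8 | 1.08 | 1.00 |
| 30% | 40% | 9.5% | 0 | 1.00 | 1.00 |
| 35% | 44% | 0.039/0.44 = 8.9% | −0.6 | 0.93 | 1.00 |
| 40% | 48% | 0.040/0.48 = 8.3% | −1.2 | 0.88 | 1.00 |

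With a true RR of 0.50 in everyone, the intervention-arm numerator is halved. At *a* = 15%, (0.0175/0.28)/0.095 = 0.66. At *a* = 30%, the RR is 0.50. At *a* = 40%, (0.020/0.48)/0.095 = 0.44. So a real benefit can be understated or overstated.

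**Step 4. Discharge coding**

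No arithmetic is offered. The documents give no coding rate and do not say how codes are assigned. The argument is structural only: coding is fixed at the end of the stay, so it can reflect a course that the intervention is meant to alter.

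**The case against.** Several points on the other side are sound.

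- **Reach.** The primary analysis is intention-to-treat on all randomized patients. The two subset analyses are labelled secondary and sensitivity, and no stopping rule or sample size depends on them. This stands. A reader might infer that the main result is compromised; it is not.
- **The bias is conditional.** A reader might infer that both comparisons are biased by construction. They are biased only if allocation shifts ICU admission or coding, and no statement in the documents shows that it does. The row at *a* = 30% makes this plain. But the plan cannot assume stable admission while testing it as an outcome, and a non-significant difference in admission would not show that the same kinds of patients were admitted.
- **Size.** The inputs are assumed. With 1001 per arm and ICU shares of 40% and 32% (about 400 and 320 patients, pooled mortality 74/720 = 10.3%), the standard error of the difference is √(0.103·0.897·(1/400 + 1/320)) ≈ 2.3 points, larger than the 1.75-point shift. It is also tempting to set such shifts against the 3-point design difference. That is the wrong benchmark, because it belongs to the whole randomized population; halving 9.5% would be 4.75 points.
- **Coding.** A reader might infer that discharge codes depend on organ failure or death during the stay. The documents do not say so; they support only that coding comes last.
- **Definition of ICU.** Table 2, footnote a, records admission from the ED to an ICU. If that variable is used, the window for the alert to act is shorter, but ED disposition still normally follows the saline order. A patient whose first saline order came in the ICU would be selected before randomization, yet the stated rationale of exposure in both settings does not describe that patient.
- **Baseline severity is already covered.** The SOFA-quartile interaction is in the plan. That is correct, and it is why the fix relies on it.

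**Conclusion.** The point holds as a matter of design. Both analyses restrict the mortality comparison to patients identified by events settled after randomization, one of which is a trial outcome, and the article gives no caveat. If allocation changes ICU admission or coding, the subset contrasts no longer compare like with like, and the distortion can go either way.

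Its size cannot be derived from the documents. On the assumed strata, with no effect on death, the ICU-only RR ranges from 0.88 to 1.32; those values show direction and plausibility, not an estimate. For discharge coding no size can be offered at all.

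The consequence is limited to interpretation of two subordinate analyses. The primary comparison, its test and the sample size are untouched. The change is worth making because it is cheap and keeps a contrast that randomization may not protect from being read as a treatment effect.

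**What to change.** 1. Make the already planned interaction of treatment with SOFA, in all randomized patients, the supportive analysis on severity. State that SOFA is the value at randomization. SOFA as a continuous modifier could be added.
2. Keep the ICU-admitted and discharge-coded subsets if wanted, but report them descriptively: deaths and denominators by arm, with no treatment-effect p value.
3. Show ICU admission and sepsis-coding rates by arm beside them, so that the reader can see whether selection differed.
4. State that neither subset will be used as support for efficacy, and make the change before unblinded results are seen.

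**Cost.** This changes analysis wording and uses data already extracted; enrolment, sample size and the primary test stay as they are. The real loss is an inferential estimate in patients exposed to the alert in both the ED and the ICU. The baseline-severity analysis answers a related question, not that one.
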